**Figure 1 F1:**
[figure not shown]
Experimental design diagram.

The sample size was determined by an a-priori power analysis using the G^*^Power3 software for Mac (72) following the indications of Beck (73). The effect size value used was: d = 0.70 with a total sample size of 30, based on a study of WB-EMS training on hip circumference in postmenopausal women (60), with two levels for the between-subject factor (EX+WB-EMS, EX), three levels for the within-subject factor (Baseline, 10 weeks, 6 months), alpha error probability set at 0.05 and a power of 0.80. This analysis indicated a minimum total sample size of 22 participants. Considering a dropout rate of 25%, 14 participants per arm will be required. In order to check the minimum effect size to which the model will be sensitive, a sensitivity analyses with the overestimated sample size assuming a 25% of dropout rate (*n* = 28) was done. The power and alpha values used were 0.80 and 0.05, respectively. The model will be sensitive enough to detect effects as small as d = 0.60.

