### Statistical Procedures

After checking normality and homogeneity assumptions, the effectiveness of different training programs on quantitative dependent variables will be assessed by a 2 × 2 mixed ANOVA. Group training intervention (“EX+WB-EMS,” “EX”) will be included as between-subjects factor, improvement (“10 weeks from Baseline,” “6 months from Baseline”) will be included as the repeated within-subjects factor, and group ^*^ improvement will be included to account for the interaction effects. Whenever a significant main effect or interaction will be observed, Bonferroni's *post hoc* correction will be used to aid interpretation of these main effects or interactions, either between-subjects factor at whatever time point or within-subjects factor at whatever group (102, 103). Hedge's *g* effect size (*g*) will be calculated and interpreted as follows *g* < 0.20 = trivial, *gfrom*0.20*to*0.50 = *mild, g* from 0.50 to 0.80 = moderate and *g* > 0.80 = large (104). Whenever the data fails to meet assumptions, robust methods will be performed following procedures of (105) and the explanatory measure of effect size (ξ) will be calculated and interpreted as suggested by (106). Values of ξ = 0.10, 0.30, and 0.50 correspond to small, medium, and large effect sizes, respectively. The qualitative ordinal variables will be analyzed with a 2 × 2 rank-based ANOVA following directions from (107). Significance level will be set at α= 0.05. The statistician will be blinded to both groups during data analyses. Intention-to-treat analysis will be performed for the primary and secondary outcomes. If necessary, a multiple imputation technique will be used to handle missing data. All analyses will be performed with JASP (version 0.11.1; JASP Team (2019), University of Amsterdam, the Netherlands) and with statistical software R Core Team (2019) for Mac and WRS2 package (108).

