To verify the effectiveness of WB-EMS, it is essential the isolation of its effects from the ones produced by voluntary contraction. In some of the previous studies, the control group received an intervention that was not equivalent to the one applied in the experimental group (58, 109–112). This procedure prevents the analysis of the WB-EMS's effect by itself. In other studies, the control group did not receive any type of intervention (64, 113), which prevents comparability between treatments. Another study compared two different types of training with WB-EMS, which only allowed the comparison of one treatment with another but prevents the analysis of the effect of the WB-EMS by itself (66). Other studies designed interventions whose control group carried out exercises of the same nature as the experimental group, but their training did not match the volume and frequency of training loads (58, 60, 114, 115). The protocol of the present study intends to carry out an experimental phase in which the interventions of both groups are completely comparable in terms of type of movements and training volume (116–118). It will allow identifying precisely the isolated effect of the WB-EMS.

The expected effects of our WB-EMS application protocol related to the development of physical fitness are based on those found by (112) when carrying out a 12-weeks training program with sedentary men. The authors observed that, except for slight improvements in some physical variables, the changes caused by the WB-EMS training were not superior to those of other exercise programs. Similar results were found by (116) in physically active women. The authors concluded that after 4 weeks of intervention, the WB-EMS training could serve as a reasonable but not superior alternative to classic training regimes. On the basis of this finding, it could be considered that the WB-EMS could be an adequate methodology to guarantee the training intensity necessary to cause positive adaptations in the organism. While it does appear to be as effective as other methodologies such as high-intensity interval training (HIIT), WB-EMS could be a good tool in order to reach the intended training intensity with the absence of abrupt movements and high resistance loads. Thus, it would be an adequate approach to postmenopausal women's physical training.

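### The stated 80% power for d = 0.70 with 22 participants belongs to a three-level within-subject calculation, not to the between-arm test that the protocol plans

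*Protocol article*

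**What the plan says.** In the protocol article, under Methods/Design, Experimental Approach (the paragraph after Figure 1), the effect size is "d = 0.70 with a total sample size of 30, based on a study of WB-EMS training on hip circumference in postmenopausal women". The calculation is set up "with two levels for the between-subject factor (EX+WB-EMS, EX") and "three levels for the within-subject factor (Baseline, 10 weeks, 6 months), alpha error probability set at 0.05 and a power of 0.80". Its result: "This analysis indicated a minimum total sample size of 22 participants". Then: "Considering a dropout rate of 25%, 14 participants per arm will be required". A sensitivity analysis at n = 28 with the same alpha and power gives d = 0.60 as the smallest detectable effect. The paragraph does not say which F test was powered (group, time or interaction), which correlation between repeated measures was used, or which SD the d refers to.

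Under Statistical Procedures, "the effectiveness of different training programs on quantitative dependent variables will be assessed by a 2 × 2 mixed ANOVA". The between-subject factor is arm. The within-subject factor has two levels, both changes from baseline: at 10 weeks and at 6 months. The group × improvement interaction is included, and Bonferroni comparisons follow significant effects. No factor with baseline as a level is analysed.

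The Discussion, reviewing earlier trials in which both arms did exercise of the same kind, includes reference 60, the source of d = 0.70, among those where "their training did not match the volume and frequency of training loads (58, 60, 114, 115").

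**The concern.** Once the outcome is change from baseline, the question whether WB-EMS adds anything is answered by the group effect. The interaction in that model asks only whether the arm difference changes between 10 weeks and 6 months. If WB-EMS gives a benefit that is fully sustained, the interaction is zero and the whole effect sits in the group term. Power calculated for a within-type test over three time points does not carry over to that term, because the two tests depend on the correlation in opposite directions: a higher correlation between measures raises power for a within-type test and lowers it for a between-subject test.

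The stake is how a null result is read. The Discussion already expects WB-EMS to be no better than other programmes and describes it as apparently as effective as interval training. A non-significant arm difference could be presented as support for that view with 80% power cited behind it, when the planned comparison may have much less.

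A second problem concerns the effect size. The trial matches the two arms so as to isolate the WB-EMS effect, but d = 0.70 comes from a study that the protocol itself describes as unmatched.

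**Working it through.** **Inputs.** From the sample-size paragraph: d = 0.70, so f = d/2 = 0.35 for two equal groups; alpha 0.05; power 0.80; three within-subject levels; N = 22 and 28; dropout 25%, so 28 × 0.75 = 21 expected completers. From Statistical Procedures: two within-subject levels (improvements) and alpha 0.05. The correlations and the SD scale of d are not in the document; they are assumptions here and are varied.

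**1. Reproducing the stated figures.** Take a within-type F test with three levels: df 2 and 2(N − 2), noncentrality λ = d²N.
- N = 22: λ = 0.49 × 22 = 10.78, power 0.815. N = 21 gives 0.794, so 22 is the minimum.
- N = 28: power 0.80 is reached at d = 0.604, matching the stated 0.60.

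This λ arises in more than one way. With λ = f²·N·3/(1 − ρ), f = 0.35 and ρ = 0.25: 0.1225 × 3/0.75 = 0.49 per participant. It also arises if 0.70 is entered directly as f with λ = f²N. With two groups, the time main effect and the group × time interaction share the same λ and df, so the arithmetic cannot tell them apart.

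**2. Trying a between-arm test with three measures.** λ = f²·N·3/(1 + 2ρ), df 1 and N − 2, at N = 22:

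| ρ | λ | Power | Detectable d at N = 28 |
|---|---|---|---|
| 0 | 8.09 | 0.77 | 0.64 |
| 0.25 | 5.39 | 0.60 | 0.78 |
| 0.5 | 4.04 | 0.48 | 0.90 |

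Neither 22 nor 0.60 comes out, even with no correlation.

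**3. The planned group effect, d in SDs of the improvement score.** With two improvements correlated r: λ = f²·N·2/(1 + r), df 1 and N − 2. Example: N = 22, r = 0.5 gives 0.1225 × 22 × 2/1.5 = 3.59, power 0.44.

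| N | Power, r = 0.3 | r = 0.5 | r = 0.8 | Detectable d at 80% (r = 0.3 to 0.8) |
|---|---|---|---|---|
| 21 | 0.47 | 0.42 | 0.36 | 1.04 to 1.22 |
| 22 | 0.49 | 0.44 | 0.38 | 1.01 to 1.19 |
| 28 | 0.60 | 0.54 | 0.47 | 0.89 to 1.04 |

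The 10-week comparison alone (two-sample t test, d = 0.70) has power 0.35 at 11 per arm and 0.43 at 14 per arm.

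**4. The planned group effect, d in single-visit SDs.** Assume the same correlation r between any two visits and an arm difference of 0.70 at both later visits. The SD of a change is √(2(1 − r)) visit SDs and the two changes correlate 0.5, so λ = [0.35²/(2(1 − r))]·N·2/1.5.

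| r between visits | Power, N = 22 | Power, N = 28 |
|---|---|---|
| 0.25 | 0.31 | 0.39 |
| 0.5 | 0.44 | 0.54 |
| 0.7 | 0.64 | 0.76 |
| 0.8 | 0.81 | 0.90 |
| 0.9 | 0.98 | 1.00 |

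The correlation that reproduces 22 with f = d/2 is 0.25. On this scale, that value would give the group effect 0.31.

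**The case against.** The best defence is that the planned model re-expresses the same information. Improvements at 10 weeks and 6 months are the two contrasts with baseline, so the group effect and the group × improvement interaction together span the 2-df group × time space. That stands, and it would be wrong to say that the powered contrasts are absent from the analysis. But power for a joint 2-df test is not power for the one term that carries the treatment conclusion.

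Four stronger readings are tempting, and the documents do not support them.
- A reader might infer that the trial was powered for the interaction at a correlation of 0.25. The paragraph names neither. The time main effect, or 0.70 entered as f, fits equally well.
- A reader might infer that true power is about 35–45%. That needs d on the improvement-score SD, N = 22 and a correlation of 0.5 or more between the two improvements.
- A reader might infer that a true d = 0.70 would be missed more often than found. At 28 participants and correlation 0.5 the power is 0.54. On the single-visit scale with high correlation it is well above 0.80, and the effect need not be sustained: at r = 0.85 the 10-week contrast alone has 0.81 at 22.
- A reader might infer that d = 0.70 is optimistic. The Discussion says only that training in the source study was not matched. It gives no direction.

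The calculation is not an arithmetic slip either, since its figures reproduce.

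**Conclusion.** The sample-size paragraph and the analysis section describe different tests, and the stated power is not that of the planned arm comparison. This part rests on the text and on the reproduction, and needs no assumption about which F test was chosen.

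How far power falls short is conditional. On the improvement-score scale, none of the correlations from 0.3 to 0.8 brings the group effect near 80%: it is at most 0.60 even with all 28 retained, and the smallest detectable d is about 0.9 to 1.2 across 28 randomised and 21 completers, against the stated 0.60. On the single-visit scale with a sustained effect, 80% at 22 participants is reached only with a between-visit correlation of about 0.8 or more. Such a correlation may hold for some outcomes, but the protocol does not state one. No single power figure should therefore be put in place of the 80%.

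Separately, d = 0.70 is not an estimate of the isolated WB-EMS effect by the protocol's own account of its source.

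**What to change.** Rewrite the sample-size paragraph under Experimental Approach so that it:
1. names the test that carries the conclusion, namely the group effect of the model in Statistical Procedures;
2. states whether d is in SDs of the improvement score or of a single visit, and which correlation is assumed;
3. replaces the claims of 80% power at 22 and sensitivity to d = 0.60 with the power and detectable d of that test at 28 randomised and about 21 completers, as a range over the correlation;
4. notes that d = 0.70 comes from a study with unmatched control training and so does not estimate the isolated effect, without asserting a direction.

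The 80% figure should not be cited in the trial report to read a non-significant arm difference as evidence of no superiority or of equal effectiveness.

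The cost is one reworded paragraph and, probably, a less favourable stated power. Whether the sample size should also change is for the sponsor to decide once the test, scale and correlation are fixed.

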## Abstract

**Background:** Age-related problems such as chronic diseases, functional limitation and dependence, reduce the quality of life in the elderly, and increase public spending in health. It has been established that physical activity plays a fundamental role in the health of the elderly. The whole body electromyostimulation (WB-EMS) could be a successful methodology as high-intensity training to improve the physical fitness of older people.

**Methods:** A minimum of 13 women between 55 and 70 years old will be randomized in two groups. The exercise with WB-EMS group (EX + WB-EMS) will conduct a resistance strength training program with superimposed WB-EMS while the exercise group (EX) will perform only resistance strength and aerobic training. Balance, strength, flexibility, agility, speed, and aerobic performance (EXERNET battery and progressive resistance test), as well as body composition, blood parameters and physical activity reporting (IPAQ-E) will be assessed to analyze the effects of whole body electromyostimulation in the physical fitness and the health in postmenopausal women.

**Discussion:** Innovative and scientifically well-designed protocols are needed to enhance the knowledge of the body's responses within this training methodology which is being used by a big quantity of population. This trial will provide evidence on the effectiveness of whole-body electromyostimulation in physical fitness and health in elderly women.

**Trial Registration:** ISRCTN15558857 registration data: 27/11/2019 (retrospectively registered).

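### The number to randomise is inconsistent (13 in the Abstract, 14 per arm in the Methods), 28 does not cover the stated 25% dropout, and d = 0.60 holds only at full retention

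*Protocol article*

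**What the plan says.** The sample-size paragraph (Methods/Design, Experimental Approach, after Figure 1) describes a G*Power calculation for a repeated-measures design. Its stated inputs are:

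- effect size: "The effect size value used was: d = 0.70 with a total sample size of 30" (taken from a cited study)
- groups: "two levels for the between-subject factor (EX+WB-EMS, EX"
- time points: "three levels for the within-subject factor (Baseline, 10 weeks, 6 months"
- error rates: "alpha error probability set at 0.05 and a power of 0.80"

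The result, and the step from it to the number to randomise, reads: "This analysis indicated a minimum total sample size of 22 participants. Considering a dropout rate of 25%, 14 participants per arm will be required". That is 28 women in total. A sensitivity analysis is then run on the full 28 and concludes: "The model will be sensitive enough to detect effects as small as d = 0.60".

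The Methods paragraph of the Abstract gives another figure: "A minimum of 13 women between 55 and 70 years old will be randomized in two groups".

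The article states neither the correlation among repeated measures nor a sphericity correction.

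**The concern.** Three figures that should agree do not.

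- **Number to randomise.** The Abstract and the Methods give different minimums, and nothing in the article links them.
- **Dropout allowance.** The Methods inflate 22 by a quarter. Losing a quarter of the inflated number then leaves fewer than 22.
- **Detectable effect.** The value of 0.60 is presented as what the model will achieve, but it is computed as if no one were lost. The same paragraph plans for a quarter to be lost.

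At stake is whether the trial has one target against which its recruitment can be judged, and whether readers are led to expect more sensitivity than the plan's own dropout assumption allows.

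**Working it through.** **1. Dropout (article figures only)**

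Inputs: 22 evaluable, 25% dropout, 14 per arm.

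- The plan's figure is reproduced by n x (1 + dropout): 22 x 1.25 = 27.5, rounded up to 28; per arm 11 x 1.25 = 13.75, rounded up to 14.
- Check: 28 x (1 - 0.25) = 21, which is below 22.
- Dropout that 28 can absorb while keeping 22: (28 - 22)/28 = 6/28 = 21.4%.
- Inflation that preserves 22, n/(1 - dropout): 22/0.75 = 29.3, so 30 with equal arms; per arm 11/0.75 = 14.67, so 15. Then 30 x 0.75 = 22.5.

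**2. Abstract against Methods (article figures only)**

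- 13 in total is below 22 and less than half of 28.
- 13 per arm would be 26, which differs from 28; 26 x 0.75 = 19.5, again below 22.

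**3. Power and detectable effect (needs an assumption)**

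Test: group-by-time interaction, noncentral F, with f = d/2, k = 2 groups, m = 3 time points, lambda = f^2 x N x m/(1 - rho), df1 = (k - 1)(m - 1) = 2, df2 = (N - k)(m - 1), alpha 0.05 and sphericity assumed. For d = 0.70, f = 0.35.

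The correlation rho is not in the article, so I looked for values that reproduce its figures. With equal arms, rho from 0.24 to 0.29 gives a required N of 22 and a detectable d of about 0.60 at N = 28. A rho of 0.5 would give 16 instead of 22. Worked example at rho = 0.25, N = 22: lambda = 0.1225 x 22 x 3/0.75 = 10.78, power 0.815; at N = 20 power is 0.771, so 22 is the smallest even N that reaches 0.80.

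| N analysed | Power at d = 0.70, rho 0.24 to 0.29 | Detectable d at 80% power |
|---|---|---|
| 28 (no dropout) | 0.90 to 0.92 | 0.61 to 0.59 |
| 22 (stated minimum) | 0.81 to 0.84 | 0.69 to 0.67 |
| 21 (28 less 25%) | 0.79 to 0.82 | 0.71 to 0.69 |
| 13 (Abstract, no dropout) | 0.54 to 0.57 | 0.93 to 0.90 |

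So 0.60 is the value with all 28 analysed. With the planned dropout, the detectable effect returns to about the 0.70 on which the trial was sized.

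**The case against.** The best defence is about weight. The shortfall is one expected completer. At an assumed correlation of 0.26, which reproduces both 22 and 0.60, 21 completers still give power of 0.80. A reader might infer from 21 < 22 that the trial is materially underpowered. The figures do not support that. The allowance is misstated, but the loss is slight.

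The sensitivity statement says openly that it uses the inflated 28, and 0.60 is about right for that number. Statistical Procedures also plans intention-to-treat analysis, with multiple imputation if necessary, which could keep all 28 in the analysis set. This stands only in part. Imputation does not in general restore the information lost with unobserved outcomes, and by inflating 22 the plan itself treats dropout as a loss. The fair criticism is that 0.60 is a best case not labelled as one.

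The 13 may be a slip, perhaps for a per-arm number. A reader might infer that recruitment could stop at 13, but the operative Methods text plainly requires 14 per arm, so this is a reporting conflict and not evidence of a smaller trial. A reader might also gauge 13 women by a two-sample t-test (7 against 6, power about 0.21 at d = 0.70). That is not the test on which the trial was sized: by it the plan's own 22 and 28 give only 35% and 43%. The comparable interaction-test power is 0.54 to 0.57.

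Finally, the correlation range is fitted from the plan's outputs. It is not a plan setting and should not be cited as one.

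**Conclusion.** The point holds, with parts of unequal weight.

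- **Abstract conflict:** the clearest error. The minimum of 13 agrees with no other figure, read as a total or per arm. It rests on no assumption.
- **Dropout allowance:** wrong as written, also without assumption. Twenty-eight covers 21% dropout, not 25%. The effect on power is minor.
- **Detectable effect:** 0.60 is valid only if all 28 are analysed. With 21 completers it is about 0.69 to 0.71, so the implied margin over the design effect of 0.70 disappears. This rests on the interaction test with three time points, sphericity, and assumed correlations of 0.24 to 0.29.

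These are errors in stated sample-size figures that should be corrected. They do not show that the design fails.

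**What to change.** 1. State one total to randomise, and use it in both the Abstract and the sample-size paragraph.
2. Choose one of two wordings for dropout. Either keep 28 (14 per arm) and say that it allows 21% dropout, leaving 22 completers, and that 21 would complete at 25%; or keep the 25% allowance and write 30 (15 per arm).
3. Label d = 0.60 as the value with all 28 analysed, and add the detectable effect at the expected number of completers, recomputed with the correlation actually entered in the software and stated in the text. Alternatively, drop the sensitivity claim. The 0.69 to 0.71 above should not be copied in as a plan value, because it depends on an assumed correlation.

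Cost: wording only if 28 is kept; two more women if 30 is chosen. The design and the analysis do not change.

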### Participants

The target of this recruitment is post-menopausal women between 55 and 70 years old (400 subjects) with a sedentary lifestyle at least 4 months prior to the study. They will be enrolled in the Ekke sports center in Lleida (Spain). They will be contacted by phone call to be informed about the nature of this study. All of them will be invited to attend an informational meeting where more details will be given on the benefits and possible risks that their participation in the project might entail. The subjects who show interest in their participation will be recruited, according to the exclusion criteria. They will be allocated and informed about their assigned arm by phone call by an external collaborator.

According to the shelf reporting in the IPAQ questionnaire of weekly physical activity, participants should be in a sedentary situation according to the scales provided by the Eurobarometer (74). Those who suffer from heart disease, metabolic disorders, tumor processes, or neurological disturbances will be excluded from this study. All participants will be informed of the details of the study and will sign an informed consent form before starting the investigation. The protocol of this study has been approved by the ethical committee of the Arnau of Vilanova's University Hospital, Lérida, (Spain). Participants will be informed of their voluntary participation. Taking into account the possible discomfort which WB-EMS could generate in the participants, they will be informed of their right to withdraw from the study without any prejudice or harm. The deterioration of the participant's health or any accident that could influence the correct development of the treatment will be reasons that will lead to their exclusion at any stage of the intervention. They will be also assured of their anonymity and the reporting of their views in aggregate form to protect their identities.

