			**(10 weeks)**		
**TIME POINT**	**T-1**	**T0**	**T1**	**T2**	**T3**
Eligibility	x				
Informed consent	x				
Randomization	x				

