**ASSESSMENTS**					
Physical fitness: Balance, leg flexibility, arm flexibility, leg strength, arm strength, agility, speed, cardiovascular endurance		x		x	X
Mean velocity (m·s-1) and the mean power of exertion (w)		x		x	x
Body composition: Weight (kg), height (cm), body mass index, body fat percentage, fat mass (kg), Visceral fat (kg), lean mass (kg), Abdominal fold, Contracted arm fold, waist perimeter, hip perimeter and Sum six folds (%).		x		x	X
Blood test: Creatin Kinasa, HDL cholesterol and triglycerides, Sodium and potassium, Thyroid Stimulating Hormone (TSH), Glycohemoglobin A1c (HbA1c)		x		x	X
Lifestyl & Health behavior: Physical activity questionnaire (IPAQ): Vigorous physical activity (AFV), Moderate physical activity (AFM) or Walking		x		x	x

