8. Cardiovascular resistance: “6-Min Walk Test.” In a circuit of 46 meters delimited by cones, the distance in meters that each participant will be able to cover walking for 6 min will be registered.

In addition to the mentioned evaluations, a progressive resistance test (PRT) (86) will be carried out to make a more accurate assessment of the strength development. The PRT permits simultaneous direct calculations of strength (N), velocity (m·s-1). and power (w), produced with different loads, and at the same time. Taking into account that as a consequence of aging, losses in strength are observed mostly in the type II fibers (87), the mean velocity and the mean power of exertion will be assessed in this study.

Following the PRT test protocol, we will assess the mentioned variables with the execution of 6 to 8 series of 2 to 3 repetitions in squat and bench press, applying the maximum acceleration possible, alternated with rest intervals of 2–5 min. The rest period is proportional to the intensity and duration of the effort, to avoid the prediction errors caused by the accumulated fatigue. The load will be increased progressively with the series. For each magnitude of weight lifted, it is necessary to select the repetition with which the highest values of average velocity and power are reached, as this factor expresses the highest mechanical efficiency of the exercise (88). In this study, the best repetition of the best series will be recorded. Then, the load in which that best series is done in the pre-test will be used in the post-test to compare the evolution of the variables after the intervention in the post-test 1 and the follow-up.

To perform this test a lineal encoder Chronojump® (Bosco–System, Barcelona, Spain) will be used in order to detect the position of the resistance during linear movements. This data permits an estimate of the range of movement, acceleration, velocity, strength and the power produced during each action (89).

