#### International Physical Activity Questionnaire (IPAQ-E)

The IPAQ-E consists of seven open questions in reference to the activities carried out by the elderly in the last 7 days. These questions evaluate the intensity by classifying it into Vigorous Physical Activity (VPA), Moderate Physical Activity (MPA), or Slight Intensity Activities (SPA). They also evaluated the frequency (days per week) as well as the time spent in each of these activities. The Total Physical Activity (TPA) is the sum of the VPA, the MPA, and SPA (100). They are considered VPA those that involve an intense physical effort and that entails breathing much more intensely than normal. MPA requires a physical effort that increases breathing at a somewhat more intense intensity than normal. Slight intensity activities include walking recreationally or for leisure (101). Only activities that last a minimum of 10 min will be considered for registration. The IPAQ-E will allow verifying the untrained condition of the participants since it gives information about the amount of physical activity which they practice in their daily life. At the same time, IPAQ-E will be the control tool regarding the amount of physical activity which the participants will practice in the time run between post-test and follow up.

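### Randomisation is scheduled before all baseline assessments and the arm is disclosed at allocation, so effort-dependent and self-reported baselines are open to knowledge of the arm

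*Protocol article*

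**What the plan says.** **Order of events.** In Table 1 (Outcomes), the row "Randomization" carries a single mark, in the pre-study column (T-1), below eligibility and informed consent in the same column. The assessment rows, among them "Physical fitness: Balance, leg flexibility, arm flexibility, leg strength, arm strength, agility, speed, cardiovascular endurance" and "Lifestyl & Health behavior: Physical activity questionnaire (IPAQ): Vigorous physical activity (AFV), Moderate physical activity (AFM) or Walking", carry their first mark at T0 and then at T2 and T3. None is marked at T-1.

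**Disclosure.** Under Participants, once interested women have been recruited against the exclusion criteria: "They will be allocated and informed about their assigned arm by phone call by an external collaborator". The section does not say when the call is made relative to T0. Experimental Approach nevertheless describes the participants as blinded, and Interventions gives the two arms different training days to protect that blinding.

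**Entry criteria.** Participants states: "According to the shelf reporting in the IPAQ questionnaire of weekly physical activity, participants should be in a sedentary situation". The IPAQ-E section repeats the use: "The IPAQ-E will allow verifying the untrained condition of the participants". Menopause Status adds an FSH threshold to the definition of postmenopausal. FSH does not appear in Table 1.

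**Use of baseline.** Statistical Procedures defines the within-subject factor as improvement from baseline, at 10 weeks and at 6 months. Physical Fitness says that the load of the best pre-test series in the progressive resistance test is used again at the later tests.

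**The concern.** A baseline measurement is safe from influence by the allocation only if it is taken before the allocation is known. Here the scheduled order is the reverse. A woman who has just learned that she did, or did not, receive the electrostimulation arm may try harder or less hard on a maximal test, or report her recent activity differently. The direction cannot be predicted.

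This matters more here than in many trials for two reasons. The analysis is built on change from baseline, so an affected baseline is the reference for both later time points. And the trial's stated purpose, in the Discussion, is to isolate the effect of WB-EMS from that of voluntary exercise, which needs arms that are comparable at the start.

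A second matter is the timing of the entry tests. If the IPAQ or FSH result that decides eligibility were obtained only at T0, a woman could be found ineligible after she had been randomised. The documents leave unclear whether this can happen.

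**Working it through.** The point concerns sequence, and the plan gives no figure to reproduce. The check sets the sections side by side and then follows a baseline shift through the planned analysis.

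**1. Sequence as scheduled (Table 1).**
- T-1: eligibility, consent, randomisation.
- T0: first fitness tests, velocity and power tests, body composition, blood test and IPAQ.

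Randomisation therefore precedes every scheduled baseline assessment. This is stated, not inferred.

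**2. When the arm becomes known (Participants).** Allocation and notification are one sentence and one telephone step. No section delays the call until T0 is finished. Separate training days do not keep the arm hidden, because the call itself names it. That women know their arm at T0 is the plain reading, but the date of the call is not given.

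**3. Which outcomes are exposed.**
- Effort-dependent: the EXERNET tests such as chair stand, arm curl, up-and-go, brisk walk and 6-minute walk, and the progressive resistance test, which is performed "applying the maximum acceleration possible".
- Self-reported: the IPAQ-E. The Discussion uses the change in total activity from the week before the intervention to the week before follow-up as a measure of adherence to exercise.
- Not exposed by this mechanism: blood values and body composition, which do not depend on test effort.

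**4. Passage of a baseline shift into the estimate.** Let D0, D2 and D3 be the between-arm differences in mean (EX+WB-EMS minus EX) at T0, T2 and T3. The analysed differences in improvement are D2 − D0 and D3 − D0. Let knowledge of the arm add s to D0 only.
- At 10 weeks: D2 − (D0 + s) = (D2 − D0) − s.
- At 6 months: D3 − (D0 + s) = (D3 − D0) − s.
- Group main effect (mean of the two): (D2 + D3)/2 − D0 − s. The shift enters in full.
- Group-by-improvement interaction: (D3 − D0 − s) − (D2 − D0 − s) = D3 − D2. The shift drops out.

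If a fraction c of the shift is still present at a later test, the error there is −(1 − c)s. It is the full s when c = 0 and nil when c = 1.

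**5. Second route, through the test load.** The load at which a woman performs best in the pre-test is carried forward. If effort at the pre-test alters which series is best, it also alters the load of her later tests. That error need not cancel even when effort is equally affected at every visit.

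**6. Eligibility.** Participants and IPAQ-E use the IPAQ to establish sedentary or untrained status. Table 1 marks eligibility at T-1 but the first IPAQ at T0. Either a screening IPAQ is taken at T-1 and not listed, or sedentary status is confirmed after randomisation. FSH has no time point in the table, so its timing is open as well.

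**The case against.** - **Table 1 may be schematic.** As read here, both intervention rows are marked under baseline rather than under the 10-week column, so column positions may be imprecise. That is a reason for care. But T-1 is the only slot given for randomisation, it sits there consistently with eligibility and consent, and no other section gives a different order.
- **The call is not dated, and participants are said to be blinded.** Both are true, and Figure 1 was not available for this check. Knowledge of the arm at T0 is therefore a strong inference and not a stated fact. The blinding statement does not remove it, because the Participants section says outright that the arm is disclosed.
- **Eligibility comes first in the text.** Table 1 lists it above randomisation, and Participants describes recruitment against the criteria before allocation. A condensed article need not itemise screening tests. This stands. A reader might infer that the IPAQ check takes place after allocation and that ineligible women will be removed afterwards, undermining the intention-to-treat set. The documents do not say so. They show an inconsistency in timing and no more.
- **The bias is limited.** Effort that shifts equally at every visit cancels in the change score, and blood and body-composition outcomes are not affected in this way. Both stand. A reader might also want to express the bias as a share of the planned d = 0.70. That would not be sound: the effect size comes from hip circumference, which does not depend on effort, and the documents offer no figure for the size of a shift.
- **The trial may have started.** Registration was retrospective and one sentence under Interventions is in the past tense. Reordering may no longer be possible for women already randomised.

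**Conclusion.** The concern holds in a bounded form. The plan schedules randomisation ahead of every T0 assessment, joins disclosure of the arm to allocation, and contains no safeguard that keeps the arm unknown until baseline is complete. On the plain reading, the effort-dependent and self-reported baselines are taken after the arm is known. For those outcomes, a shift confined to baseline passes in full into the group main effect and into the between-arm comparison of improvement at each time point. It does not enter the interaction term. A shift that persists reduces the error and, if constant, removes it, apart from the route through the progressive resistance test load.

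The size and direction cannot be given from the documents. The conclusion assumes that Table 1 will be followed as written and that the call is made when allocation is made.

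The timing of the IPAQ and FSH is a separate inconsistency to be reconciled across Participants, Menopause Status, IPAQ-E and Table 1. It does not establish that eligibility is decided after randomisation.

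**What to change.** 1. Settle eligibility first, including the IPAQ and FSH, and then complete all T0 assessments.
2. Only then run the random number generator and make the telephone call, before the first training session.
3. In Table 1, move randomisation to after T0, and show when the screening IPAQ and FSH are obtained. If one IPAQ serves both screening and baseline, say so.
4. State this order under Experimental Approach and Participants, with the timing of the call, and reconcile the disclosure of the arm with the statement that participants are blinded.
5. If the trial already works in this order, correcting Table 1 and dating the call is enough.
6. If women have already been randomised in the scheduled order, report the actual sequence of randomisation, disclosure and baseline testing, and any exclusions made after randomisation. Statistical adjustment for baseline cannot be relied on as a substitute, because the baseline is the value in doubt.

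For women not yet randomised, the change uses the same visits, staff and call, and the cost is a reordering and a few lines of text. For women already randomised it cannot be applied, and only the reporting in step 6 remains.
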